
**Table 2 T2:** Definition of disease progression.

Definition of progression of papillary thyroid cancer under active surveillance for which salvage surgery is advised (one or more of the criteria listed below)*
1. Primary index PTC growth >3 mm (in the largest dimension), confirmed on two consecutive ultrasound exams. The 3 mm size cut off is considered reproducible (21)
2. Primary PTC growth in a location that is concerning (e.g. immediately adjacent to the trachea or in the course of the recurrent laryngeal nerve) (22)
3. Incident development of metastatic PTC to lymph nodes (confirmed on cytology or unequivocal imaging)
4. Incident development of distant metastatic PTC (confirmed on imaging or biopsy or surgical histology)

*Patients may choose to have surgery in absence of disease progression at any time point in follow-up.

Thyroid cancer-related medical records will be reviewed by study staff at least yearly, for up to 10 years, regarding thyroid cancer outcomes, treatments, and potential treatment-related complications. Patient questionnaires/interviews and communication scripts are in English for most study sites, but in (Quebec/Canadian) French for Quebec sites.

For patients recruited in the multi-centre study, a baseline self-administered written questionnaire includes demographics and medical history, a question on baseline disease management preference, as well as the following patient-reported outcomes: i) quality of life (thyroid cancer/cancer-specific - EORTC QLQ-THY34 (12) with EORTC QLQ-C30 (13) and ii) anxiety (Generalized Anxiety Disorder Screener, GAD-7) (14). Patients recruited from the original Toronto study who had previously completed a baseline questionnaire as outlined in the original study protocol (10), will not perform a repeat baseline assessment, but relevant original baseline data will be reported.

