### Statistical Analysis

Descriptive data will be presented in the surgical and AS groups for baseline demographic characteristics, medical history, initial disease management choice (surgery or AS), patients’ rationale for their choice, thyroid cancer treatments, and thyroid hormone treatment. Summaries of follow-up date will tabulate major complications of thyroid cancer surgery (i.e. clinically diagnosed hypoparathyroidism or recurrent laryngeal nerve injury beyond the first year after any thyroid cancer surgery), most recent PTC disease status, proportions crossing over from AS to surgery (and indication), and deaths (thyroid cancer-specific and overall, respectively).

The primary analysis will separately estimate the cumulative incidence of ‘failure’ of disease management (along with 95% confidence intervals) at any given time since enrolment in the AS and surgical arms, using the Kaplan-Meier method. The differences in cumulative incidence will also be calculated (with 95% confidence intervals).

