For categorial outcomes, we will report proportions with 95% confidence intervals according to AS or surgical group. For all categorical clinical outcomes for which there is a sufficient number of events for meaningful analysis, we will compare the AS and surgical groups using competing risks models. We will summarize the following secondary patient-reported outcomes in each group: i) quality of life (thyroid cancer/cancer-specific) (12, 13), ii) anxiety (14), iii) survivor concerns (16), and iv) decision regret (15) (relating to the original decision on VL-PTC disease management). The data will be reported at last available study follow-up, with data from prior time points analyzed in interim analyses, if there are sufficient patients and events for meaningful analysis. All questionnaire data will be scored as per developers, for total scores or subscale scores. Where patient reported outcomes are missing and patients are known to be alive, multiple imputation will be used, with other outcomes one the same patient at the same time or other times in the imputation model. For each questionnaire outcome, we will calculate summary statistics to characterize the cohort at the last follow-up. Analyses will be adjusted for baseline variables, including age, sex, and primary tumor size (≤ 1cm or > 1cm) as well as duration of follow-up. If sufficient data are available for meaningful analysis will examine predictors of psychosocial health outcomes (e.g. age, sex, primary tumor size) if sufficient data are available for meaningful analysis. Clinical outcomes will also be compared between men and women, if there are sufficient events.

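### Clinical events that accrue over follow-up are reported by arm as proportions with no time point, although entry is staggered and follow-up runs to 10 years

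*Protocol article*

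**What the plan says.** The Statistical Analysis section of the protocol article treats three kinds of result differently.

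- **Primary outcome.** Failure of disease management is estimated separately in each arm as a cumulative incidence "using the Kaplan-Meier method", with differences and 95% confidence intervals.
- **Categorical outcomes, by arm.** Here "we will report proportions with 95% confidence intervals according to AS or surgical group". No time point is given. The preceding descriptive paragraph also lists late surgical complications, latest disease status, crossover from active surveillance (AS) to surgery, and deaths as tabulated summaries.
- **Categorical clinical outcomes, between arms.** "we will compare the AS and surgical groups using competing risks models", but only for outcomes "for which there is a sufficient number of events for meaningful analysis". The number that suffices is not defined.

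Two further phrases bear on timing. "The data will be reported at last available study follow-up" follows the list of patient-reported outcomes. The adjustment list, which includes age, sex and tumour size "as well as duration of follow-up", follows the questionnaire summary.

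Follow-up is uneven by design. The Introduction dates the Toronto study from 2016. The eligibility section says its consenting patients will be reported together with the multi-centre recruits, and the ethics section shows some sites still awaiting approval. Study Follow-Up Assessments and Outcomes has records reviewed "at least yearly, for up to 10 years".

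**The concern.** When patients are followed for different lengths of time, the number with an event divided by the number enrolled is not the risk at any stated time. Someone enrolled last year and event-free counts the same as someone event-free at ten years. The figure rises as the cohort ages, cannot be compared with published risks at fixed times, and falls below the risk at the long horizons the study is meant to inform.

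The plan recognises this for its primary outcome and for modelled comparisons. The gap is the reported by-arm estimate for secondary clinical events, above all where events are too few for a model, since the proportion and its interval may then be the only result given. The Discussion says the results are to support counselling on long-term outcomes, which needs risks tied to a time.

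**Working it through.** The plan gives no expected figure for these secondary outcomes, so there is none to reproduce. The check takes event rates from the document and assumes a constant hazard λ. The follow-up distributions are assumptions, as the document gives none.

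**Inputs from the document**
- Introduction: 5.3% tumour growth and 1.6% nodal metastasis under AS at 5 years; 5.3 + 1.6 = 6.9% if the two do not overlap.
- Sample Size Calculation: about 3% failure at 2 to 3 years (taken as 2.5 years); about 330 AS and 120 surgical patients.
- Introduction: 200 Toronto patients, leaving 450 − 200 = 250 others if all 200 consent to long-term follow-up.

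**Step 1: understatement from censoring alone**

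With follow-up uniform on (0, T), the expected proportion is 1 − (1 − e^(−λT))/(λT).
- 6.9% at 5 years: λ = −ln(0.931)/5 = 0.0143 per year. The proportion is 1 − 0.069/0.0715 = 3.5%, about half the 5-year risk.
- 1.6% at 5 years, nearer to a sparse outcome: λ = −ln(0.984)/5 = 0.00323 per year. The proportion is 1 − 0.0160/0.01613 = 0.8%, again half.
- 3% at 2.5 years: λ = −ln(0.97)/2.5 = 0.0122 per year. With follow-up uniform over 0 to 10 years the proportion is 5.85%, against true risks of 5.9% at 5 years and 11.5% at 10 years. It sits near the risk at average follow-up, well below the 10-year risk.

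**Step 2: dependence on follow-up length**

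At the same λ = 0.0122, if everyone is followed for the same time, the proportion 1 − e^(−λT) is 1.2% at 1 year, 2.4% at 2, 5.9% at 5 and 11.5% at 10.

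**Step 3: could the arms differ with no true difference?**

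Only if follow-up differs by arm. With equal hazards and 3 versus 5 years of follow-up, the proportions are 3.6% and 5.9%, a gap of 2.3 points. With equal follow-up the expected gap is zero.

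A scenario closer to the design gives Toronto patients 4 to 8 years (expected proportion 7.04%) and new patients 0 to 4 years (2.40%), with arms of 330 and 120:

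| Toronto AS of 200 | AS proportion | Surgery proportion | Gap |
|---|---|---|---|
| 142 (71%) | 4.40% | 4.64% | 0.24 points |
| 150 (3:1) | 4.51% | 4.33% | 0.18 points |
| 155 | 4.58% | 4.14% | 0.44 points |

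For the 150 row, AS is (150 × 7.04 + 180 × 2.40)/330 and surgery is (50 × 7.04 + 70 × 2.40)/120.

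**Step 4: how sparse are the outcomes?**

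At 3%, even the primary outcome gives about 330 × 0.03 = 10 events under AS and 120 × 0.03 = 4 after surgery. Rarer outcomes could well fall short of whatever number is judged sufficient for a model.

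**The case against.** The strongest reply is that the inferential work already uses time-to-event methods. The primary outcome is a Kaplan-Meier cumulative incidence with differences, and categorical clinical outcomes are compared by competing-risks models where events allow. Nodal progression under AS that leads to surgery enters the primary analysis. The document does not call the proportions crude, and a condensed article may leave the estimator for descriptive tables to a fuller document. Some categorical items, such as latest disease status, do not accrue over time, and surgical complications do not follow a constant hazard from enrolment.

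Most of this stands, and it limits the point. A reader might infer that the planned arm comparison is biased by two points or more. The document does not support that. No test on the proportions is planned, nothing shows that follow-up differs by arm, and the AS share is similar throughout (71% in the first 100 Toronto patients, 330/450 = 73% planned overall). Follow-up could still differ, because AS patients are offered indefinite follow-up at a study site while surgical patients may be treated anywhere, but that is only a possibility.

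Three things are not answered. The competing-risks sentence governs comparisons with enough events, not the by-arm estimate. Adjusting for duration of follow-up, even if it were meant for clinical outcomes, does not repair a proportion computed from censored data. And the plan does state its by-arm measure, a proportion with no time attached, so this is more than an omitted detail.

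**Conclusion.** The point holds for clinical events that accrue over follow-up, and for the by-arm estimates only. Followed as written, the plan gives these events a figure that is not a risk at any time and understates long-term risk. The shortfall is about half of the 5-year risk if follow-up is spread evenly over 0 to 5 years. That size rests on an assumed constant hazard and assumed follow-up; the direction needs only censoring.

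A spurious difference between arms is possible but not shown, and is at most about 0.4 points in the pooled scenario above. It would be smaller still for events rarer than the 3% rate used there.

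It would be wrong to read this as a flaw in the primary analysis, in the modelled comparisons, or in every categorical summary. The exposed results are the sparse secondary events, for which the proportion may be all that is reported.

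**What to change.** For clinical events that accrue over follow-up:

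- Replace the proportion with cumulative incidence by arm (Aalen-Johansen, death as the competing event) and 95% confidence intervals, at stated times with enough patients at risk, for example 2, 5 and 10 years.
- Measure surgical complications from the date of surgery, so that AS patients operated on later are counted on the same clock.
- For sparse outcomes, give the number of events, the person-years and the rate per 100 person-years by arm.
- Summarise length of follow-up by arm.

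Keep simple proportions for baseline categories, for status at a stated assessment, and for outcomes with a complete fixed window.

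This needs a change of wording and some programming, with no new data, and it brings the secondary estimates into line with the time-to-event methods the plan already uses. The price is wider intervals at late times, which show how little late information there is.

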	•Patient is unable or unwilling to consent for study follow-up procedures (e.g. due to current severe active cognitive or psychiatric impairment, substance abuse, or other reasons)

*****Changes in the original Toronto protocol, approved by the University Health Network Research Ethics Board (April 7, 2020) and incorporated in the pan-Canadian at onset of the study include: not mandating central cytopathology review (i.e. may be performed at the discretion of the investigator if there is any uncertainty or concern about the original review, but not mandating this due to limited value with some patient delays observed in the Toronto study), not excluding patients who have mild thyroid or parathyroid disease that does not meet established absolute indications for surgical treatment (e.g. hyperthyroidism under control with medication, mild primary hyperparathyroidism), excluding patients with any prior thyroid surgery (not just thyroid cancer surgery, as prior partial thyroidectomy could confound results at long-term follow-up, although no patients with prior thyroid surgery have been enrolled in the Toronto study), and permitting patients who have had a recent diagnosis, treatment, or active surveillance of another malignancy to participate in the study if the expected survival of the other malignancy is > 1 year (as patients with other malignancies, including those under active surveillance for other low risk cancers, have expressed interest in this study).

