Patient recruitment at all study sites is focused in participating thyroid cancer clinics, although eligible patients may be referred by healthcare providers or refer themselves by contacting a study centre. Screening for eligibility in consenting patients is performed by a research assistant, under the supervision of a site investigator. All patients are required to have at least one consultation by a thyroid cancer surgeon (at any institution) such that the type of surgery that would be recommended for the particular case, as well as potential complications, are explained in detail (as per usual clinical practice of the surgeon). Participants are informed about the options of AS and surgery and provided written handout summarizing the relevant literature on both AS and surgical options, and given the opportunity to meet with a study physician to discuss the provided information and obtain answers to any related questions. Patients are free to make their own disease management choice and the clinical disease management course (i.e. surgery or AS) is not assigned by the investigators in the study. Baseline neck imaging studies are reviewed by a study investigator experienced in interpretation of neck ultrasound or a radiologist with expertise in ultrasound who is familiar with the study, to confirm eligibility. Training on evaluation of ultrasounds for baseline assessment and follow-up has been provided at a national investigator meeting ([name], [name]) and will be revisited during the course of the study at yearly (or more frequent) investigator meetings. The central study co-primary investigators ([name], [name]) are available to advise and support the other investigators throughout the study. A REDCap database has been developed by the THETA Group at University Health Network, for centralized electronic collection of data entered by research staff at each study site.

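### The covariates named for the patient-reported comparisons omit the comorbidities that the widened entry rules admit, leaving possible, probably modest, residual confounding

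*Protocol article*

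**What the plan says.** **Entry.** The footnote to Table 1 lists changes carried into the multi-centre study. One is "permitting patients who have had a recent diagnosis, treatment, or active surveillance of another malignancy to participate in the study", provided expected survival from that malignancy is over one year. Another is "not excluding patients who have mild thyroid or parathyroid disease that does not meet established absolute indications for surgical treatment", with the examples "hyperthyroidism under control with medication, mild primary hyperparathyroidism". As a reason for the first change, the footnote says that "patients with other malignancies, including those under active surveillance for other low risk cancers, have expressed interest in this study".

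**Choice of arm.** The recruitment section says "Patients are free to make their own disease management choice". The Sample Size Calculation section expects the surgical arm to allow controlled comparisons of the secondary outcomes.

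**Adjustment.** The Statistical Analysis section says "Analyses will be adjusted for baseline variables, including age, sex, and primary tumor size" (size in two bands, at or below 1 cm and above 1 cm), together with duration of follow-up.

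**Available data.** For multi-centre recruits, "a baseline self-administered written questionnaire includes demographics and medical history", alongside the baseline quality-of-life and anxiety instruments. The only use stated for medical history is a summary by group: "Descriptive data will be presented in the surgical and AS groups for baseline demographic characteristics, medical history". The survivor-concerns scale is listed at yearly follow-up but not at baseline.

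**The concern.** A second cancer, or a treated endocrine disorder, can plausibly move a general cancer quality-of-life score, an anxiety score or a score of worry about cancer. The arms are self-selected, so nothing in the design balances these conditions between them. The covariates that are named (age, sex, tumour size band, follow-up time) do not measure them.

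If such patients are more common in one arm, part of any difference between AS and surgery on these scores may belong to the other condition. The same mechanism can hide a real difference. Enlarging the sample, which the yearly re-evaluation allows, would not shrink this bias. The protocol's own change of entry criteria makes the confounder foreseeable, and the baseline questionnaire collects the history needed to handle it.

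Pooling adds a smaller issue. Data from the original Toronto study are reported with the new recruits, and any Toronto patient enrolled before the April 2020 change entered under different rules on these two conditions.

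**Working it through.** **The plan's own figure.** The article gives no number on this point. Its only sample-size target, 328 AS patients for an expected 95% half-width of 2% around 3%, belongs to the primary outcome. It reproduces as 327 with the exact (Clopper-Pearson) interval and plays no part below, except that the planned arm sizes come from the same section.

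**Inputs from the article.** 330 AS and 120 surgical patients.

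**Assumed inputs.** The share of patients with another condition in each arm, its effect on a score, and the SD of the score. None of these is in the article.

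**Formula.** Bias in the arm difference = (share in AS − share in surgery) × effect of the condition on the score. The shares should be read as those remaining after the named adjustments.

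**Precision.** SE in SD units = √(1/330 + 1/120) = 0.107. The 95% half-width is 1.96 × 0.107 = 0.21 SD, and the difference detectable with 80% power is 0.30 SD. With SD 20 on a 0–100 scale, SE = 20 × 0.1066 = 2.13 points. These figures assume complete questionnaires. With fewer responses the SE rises and the bias is smaller relative to it.

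**Illustration in points (effect 10, SD 20).**
- 10% v 5%: 0.05 × 10 = 0.5 points; 0.5/2.13 = 0.23 SE.
- 15% v 0%: 0.15 × 10 = 1.5 points; 1.5/2.13 = 0.70 SE.

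**Wider range in SD units.**

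| Share AS v surgery | Effect 0.3 SD | Effect 0.5 SD | Effect 0.8 SD |
|---|---|---|---|
| 10% v 10% | 0 | 0 | 0 |
| 10% v 5% | 0.015 | 0.025 | 0.04 |
| 15% v 5% | 0.03 | 0.05 | 0.08 |
| 20% v 5% | 0.045 | 0.075 | 0.12 |
| 5% v 15% | −0.03 | −0.05 | −0.08 |

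The largest entry is 0.12/0.107 = 1.1 SE, still inside the 0.21 SD half-width. The last row shows that the sign reverses if the imbalance runs the other way.

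**Effect on a test.** With no true difference, a two-sided 5% test whose estimate is shifted by 0.70 SE rejects about 11% of the time. Shifted by 1.1 SE, it rejects about 20% of the time.

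**Could a baseline score do the work instead?** For quality of life and anxiety, multi-centre recruits have a baseline score that could absorb part of the imbalance, although the article does not name it as a covariate. For survivor concerns no baseline measure is listed, so this route is closed.

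**The case against.** The strongest reply is that the adjuster list opens with the word including, so it is not closed. A journal article may also leave the full covariate set to a protocol or analysis plan that is not shown. That stands as far as it goes: the article does not rule these covariates out and does not contradict itself. But it does not simply defer the matter. It names covariates, and an analyst who used only those would meet the text while omitting a condition that the new entry rules make foreseeable.

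Further replies also hold in part:
- **Imbalance is not shown.** A reader might infer that patients under surveillance for another cancer will choose AS. The footnote says only that they are interested in a study that offers both options.
- **Severity is limited.** Patients unfit for surgery through severe comorbidity are excluded, and the admitted endocrine disease is mild or controlled.
- **Not every instrument is equally exposed.** The thyroid-specific module and the decision regret scale, which refers to the original decision, are less obviously affected. That the other instruments cannot separate the two diseases is plausible, but it depends on item content the article does not give.
- **An imbalance would be visible.** Medical history is tabulated by group, and the Discussion names the lack of randomisation as an important limitation. Neither step removes the bias from the adjusted estimate.

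**Conclusion.** The point holds as possible residual confounding of secondary patient-reported comparisons. It requires that the conditions differ between arms after the named adjustments and that they shift the scores. Both are plausible, and neither is established by the article. On the assumed inputs the bias runs from zero to 0.2–0.7 SE in the points illustration, and to 1.1 SE in the most extreme case tabulated. This is probably modest, and its direction is unknown. The primary outcome is untouched: failure counts treatment for progression, persistence or recurrence of the thyroid cancer.

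A reader might go further and conclude that the other illness will be reported as an effect of AS or surgery. The documents do not support this, because they give no shares and no effects, and balanced arms give no bias.

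Nor do they support saying that the whole Toronto cohort entered under uniformly narrower rules. The footnote describes an amendment to the Toronto protocol itself, no date is given for the end of Toronto recruitment, and one of the changes (excluding any prior thyroid surgery) tightened entry.

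**What to change.** In the Statistical Analysis section, add two baseline indicators to the covariates named for the adjusted patient-reported models: other malignancy (diagnosed, treated or under surveillance), and other thyroid or parathyroid disease. Add one sensitivity analysis that excludes patients with either condition. Fix both before outcome data are compared by arm, so that the choice cannot look data-driven.

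The sensitivity analysis should not be described as restoring the original Toronto entry criteria. The requirement for central cytopathology review and the rule on prior thyroid surgery changed as well.

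The cost is two extra covariates and one extra model run, with no new patients and no new data collection for multi-centre recruits. For patients from the original Toronto study, who do not repeat the baseline assessment, someone must check that the original baseline data hold these items.

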Yearly follow-up questionnaires (up to 5 years) include: an update of thyroid cancer status and thyroid cancer treatments as well as the following questionnaires: i) quality of life (thyroid cancer/cancer-specific - EORTC QLQ-THY34 (12) with EORTC QLQ-THY34 (13) ii) anxiety (Generalized Anxiety Disorder Screener, GAD-7) (14), iii) survivors’ concerns (Assessment of Survivor Concerns, ASC [1])), and iv) decision regret, relating to the original decision to undergo AS or surgery [decision regret scale (15)]. The questionnaires used in this study to evaluate quality of life and psychosocial outcomes have all been previously used in cancer populations.

For sites in the province of Quebec using French language EORTC QLQ-THY-34 (12) and ASC (16) adapted to Quebec French are not available at the time of initiation of this protocol so they will be initially omitted, with the intention of incorporating them once available (after approval of research ethics board amendments in sites in the province of Quebec).

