
Low risk PTC patients’ rationale for AS or surgery is important to understand. Our preliminary findings on patients’ rationale for AS (10) confirmed prior observations reported by D’Agostino et al. at Memorial Sloan Kettering, who reported that some patients perceived the cancer as relatively indolent and experienced concerns related to living without a thyroid or requiring thyroid hormone treatment (19). Concerns about taking thyroid hormone are commonly expressed by patients considering thyroid surgery. A recent international survey of more than 12,000 patients on thyroid hormone treatment suggested prominent dissatisfaction in about 15% of patients taking levothyroxine (20). Although only a small subset of surveyed patients had a history of thyroid cancer (346 patients), thyroid cancer patients reported a high level of agreement with a statement indicating that thyroid hormone treatment impacted their lives (20). The concerns that are expressed by some thyroid cancer patients regarding the long-term implications of thyroidectomy and thyroid hormone treatment are important for healthcare practitioners to acknowledge and formally address in the discussion of disease management choices. However, it is equally important to acknowledge that for some patients, their primary goal in managing their disease is cure of the cancer (by surgery and other treatments, if needed) (10). For informed, low risk PTC patients who are not comfortable living with the knowledge of an untreated thyroid cancer, surgery is clearly the preferred initial disease management choice (10). Appropriate disease management of small, low risk PTC should thus incorporate consideration of patients’ preferences.

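### For the AS-versus-surgery comparison of anxiety and quality of life, the baseline score is not a named covariate and the time point is not fixed

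*Protocol article*

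**What the plan says.** All places are in the protocol article.

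- **Covariates (Statistical Analysis).** "Analyses will be adjusted for baseline variables, including age, sex, and primary tumor size" (the latter split at 1 cm), and the sentence continues "as well as duration of follow-up". The list is open-ended, and no questionnaire score is on it.
- **Time point (Statistical Analysis).** "The data will be reported at last available study follow-up". For each questionnaire, "we will calculate summary statistics to characterize the cohort at the last follow-up". Earlier time points go to interim analyses where data suffice, and missing scores of patients known to be alive are multiply imputed, drawing on the patient's other outcomes at the same or other times.
- **Baseline measurement (Study Follow-Up Assessments and Outcomes).** Multi-centre recruits complete a baseline questionnaire with demographics and history "as well as the following patient-reported outcomes: i) quality of life" (QLQ-THY34 with QLQ-C30) and "anxiety (Generalized Anxiety Disorder Screener, GAD-7". Original Toronto patients do not repeat it; their relevant earlier baseline data are reported.
- **Follow-up measurement (same section).** "Yearly follow-up questionnaires (up to 5 years) include" quality of life, GAD-7, survivor concerns and decision regret. Quebec sites using French initially omit QLQ-THY34 and the survivor-concerns scale.
- **Who chooses what.** Management is not assigned by the investigators (recruitment section). The Discussion says that for "patients who are not comfortable living with the knowledge of an untreated thyroid cancer, surgery is clearly the preferred initial disease management choice".
- **Purpose.** The Sample Size Calculation says that the surgical arm makes controlled comparisons possible for secondary outcomes.

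**The concern.** In a cohort where patients choose their management, the covariates carry the burden that randomisation would otherwise carry. The article itself gives a reason for the choice, unease about leaving a cancer untreated. Anxiety and cancer-specific quality of life are outcomes that such unease could plausibly affect. Age, sex and tumour size do not measure it. A baseline GAD-7 or EORTC score comes closer and is already collected from most new recruits. If it stays out of the model, a follow-up difference between arms may only reflect a difference that was there at enrolment.

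The time point raises a separate issue. Toronto recruitment began in 2016 and its patients are pooled with later sites, so last visits will fall in different years. A contrast at last available follow-up then averages over whatever mix of years the cohort supplies and belongs to no defined time. These comparisons are secondary, but the article intends the results to inform patient counselling.

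**Working it through.** **The plan's own figures.** The article gives no power, SD, baseline gap or correlation for the patient-reported outcomes. Its sample size of 328 concerns the failure rate in the AS arm. It reproduces (327 is the smallest number whose expected exact 95% half-width at 3% is at most 2%) but does not bear on this point. From the document I use only the expected group sizes, 330 and 120, and the yearly schedule to year 5. Everything else below is assumed.

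**1. Omitting the baseline score.** Work in SD units with no true effect. Let *d* be the baseline gap between groups and *ρ* the within-group correlation of baseline with follow-up.

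- Spurious difference = *ρ* × *d*
- SE of the unadjusted contrast = √(1/330 + 1/120) = 0.107
- False-positive rate at two-sided 5% = Φ(*ρd*/SE − 1.96) + Φ(−*ρd*/SE − 1.96)

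| *d* | *ρ* | spurious difference | false positives |
|---|---|---|---|
| 0.2 | 0.5 | 0.10 | 16% |
| 0.2 | 0.6 | 0.12 | 20% |
| 0.3 | 0.5 | 0.15 | 29% |
| 0.4 | 0.5 | 0.20 | 47% |
| 0.4 | 0.6 | 0.24 | 61% |

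For scale, the difference detectable with 80% power is (1.96 + 0.84) × 0.107 = 0.30 SD. If *d* = 0, the spurious difference is zero.

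**2. The same question by simulation, with the planned duration adjustment in place.** 1,500 runs, 330 v 120, follow-up years 1 to 5 with shorter follow-up in the surgical arm, a linear time trend common to both arms, *d* = 0.3, *ρ* = 0.5:

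- adjusted for duration only: bias 0.15 SD, false positives 27%
- adjusted for duration and baseline score: bias about 0.00, false positives 5%

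With a levelling-off trend the figures are 0.15 SD and 28%, then about 0.00 and 6%. Duration therefore does not stand in for the baseline score.

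**3. Does unequal follow-up by itself bias the contrast?** Same simulation with *d* = 0. With the linear trend and no adjustment, bias is 0.10 SD with 15% false positives; once duration is a covariate, it is about 0.00 with 4%. With the levelling-off trend, 0.03 SD becomes about 0.01. The planned covariate does its job when both arms share one trend.

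**4. When the arms follow different courses.** Suppose, for illustration, that surgery has a transient effect of 0.5 SD at year 1, 0.25 SD at year 2 and none later, with no baseline gap and the same mix of last visits in both arms. The last-available contrast is the effect averaged over that mix:

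- mostly early (35, 25, 20, 10, 10% in years 1 to 5): 0.35 × 0.5 + 0.25 × 0.25 = 0.24 SD
- uniform (20% each year): 0.20 × 0.5 + 0.20 × 0.25 = 0.15 SD
- mostly late (10, 10, 20, 25, 35%): 0.10 × 0.5 + 0.10 × 0.25 = 0.075 SD

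A simulation with a linear duration term gave nearly the same values (0.23, 0.15 and 0.08). One truth gives a threefold range, set only by when patients last answered.

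**5. Where a baseline score exists.** GAD-7, QLQ-C30 and QLQ-THY34 are listed at baseline; survivor concerns and decision regret are not, and regret about a decision can have no score before it. The yearly list prints QLQ-THY34 twice, the second time with the reference number that QLQ-C30 carries at baseline. I read that second entry as QLQ-C30.

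**The case against.** The strongest reply is that the article does not exclude the baseline score. The covariate list opens with *including*, the scores are baseline variables, and a condensed article may leave the full model to an analysis plan that is not shown. This stands in part. It would be wrong to infer that the baseline score has been ruled out. But the article did choose to list covariates, and nothing commits the analysts to the one most closely tied to the stated reason for choosing surgery.

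Second, the evidence for confounding is indirect. The Discussion speaks of unease about untreated cancer, not of measured GAD-7 differences, and the article does not say whether the baseline questionnaire precedes the choice. This stands. The gap is an assumption, and so are the size and direction of any bias.

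Third, these outcomes are described as summarised in each group, and the lack of randomisation is acknowledged. However, the planned adjustment and the promise of controlled comparisons both point to a between-group contrast.

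A reader might draw four stronger conclusions that the document does not support:

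- *Unequal follow-up as such biases the contrast.* Duration is an adjuster in the same sentence, and it removed that bias in both common-trend scenarios. Informative dropout was not examined.
- *Yearly data are discarded.* Earlier time points feed interim analyses and the imputation model.
- *Duration enters as a linear term.* No functional form is stated.
- *Splitting tumour size at 1 cm is an error.* That is the microcarcinoma boundary around which the Introduction is built, and no harm from it has been shown.

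**Conclusion.** The point holds for GAD-7 and EORTC quality of life. The covariates named do not include the baseline score of the same instrument, although it is collected in multi-centre recruits and the article gives a reason to expect the groups to differ on it. With a baseline gap of 0.2-0.4 SD and a correlation of 0.5-0.6, both assumed, 0.10-0.24 SD of spurious difference remains after the named adjustments. That is one third to four fifths of the 0.30 SD detectable with 330 and 120 patients (0.10/0.30 and 0.24/0.30). It presumes that age, sex and tumour size explain little of the baseline gap.

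The time-point concern also holds, in a limited form. The last-available contrast refers to no defined year, and adjusting for duration does not resolve this if the arms follow different courses. For survivor concerns and decision regret only the time-point concern applies. The outcomes are secondary and the remedy is cheap, so this should be changed, but it does not threaten the primary analysis.

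**What to change.** In the Statistical Analysis section:

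1. For GAD-7, QLQ-C30 and QLQ-THY34, name the baseline score of the same instrument as a covariate, alongside age, sex and tumour size.
2. Model all yearly scores (years 1 to 5) in a mixed model with arm, year and arm-by-year, and report the arm contrast at one named year. Year in the model then replaces duration of follow-up as a covariate, and the named year replaces last available follow-up.
3. For survivor concerns and decision regret, report at the same named year, optionally adjusting for baseline GAD-7.
4. Correct or confirm the duplicated QLQ-THY34 entry in the yearly questionnaire list, so that baseline and follow-up instruments match.

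**Cost.** Only wording changes; no new data are needed. Where the baseline score is available, adjustment also lowers the SE, from 0.107 to about 0.107 × √(1 − 0.5²) = 0.092 or 0.107 × √(1 − 0.6²) = 0.085 SD, slightly less of a gain when the groups differ at baseline. The full gain will not be reached. Original Toronto patients do not repeat the baseline assessment, and this article does not list their baseline instruments; French-language Quebec sites initially lack QLQ-THY34. Those baseline scores must be imputed, which the planned multiple imputation could be extended to cover, or the analysis restricted to patients who have them. The plan should say which.
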